### Data Collection

Data are being collected regarding social, epidemiological, and demographic characteristics, as well as detailed information on antimalarials (type of salt, dosage, frequency, adherence during the pandemic) and rheumatic disease (diagnosis, disease activity). In addition, aspects related to comorbidities, smoking, alcohol intake, and concomitant medications are being recorded, as well as specific information about COVID-19 symptoms and main outcomes (hospitalization, need for intensive care unit, and death) in both groups (Multimedia Appendix 1).

All phone interviews are being conducted by health care professionals (eg, volunteer medical students), all previously trained by the principal investigator or subinvestigator from each rheumatology center (Figure 1). This training included a tutorial in PDF and video formats about each step of the study protocol. In addition, several WhatsApp-based groups were formed and supervised by the principal investigator, subinvestigator, or study coordinators to find the best solution for minimizing eventual problems.

**Figure 1 figure1:**
[figure not shown]
Centers participating in the study.

All patients and controls gave a verbal informed consent before participating in this cohort study. The need for signed informed consent was waived by the Brazilian National Ethics Committee (CONEP) due to the urgency of the pandemic. However, it is worth emphasizing that participation was voluntary for both groups. Research subjects will not be identified by their full name at any time and will not have their personal data disclosed.

The data are being stored on the REDCap platform, with telephone interviews performed as shown in Figure 2. Interviews with patients with invalid contact information or who did not answer the telephone after three consecutive calls at intervals of 3 days were canceled, although patients were not removed from the study. All patients will be evaluated during the closing visit (V6), unless they decline to participate, regardless of whether intermediary visits were missed (V2 to V5).

**Figure 2 figure2:**
[figure not shown]
Telephone interview schedule.

A clinically confirmed case of COVID-19 was defined according to the Brazilian Ministry of Health criteria [50] that included self-reported symptoms (fever, cough, nasal congestion, shortness of breath, malaise, myalgia, decline in general condition, and sudden anosmia and/or dysgeusia) and/or have been in contact with someone with a confirmed or suspected case of COVID-19. A positive PCR (polymerase chain reaction) test for SARS-CoV-2, via oropharyngeal and nasopharyngeal sampling or a specific confirmatory serology (immunoglobulin G and/or immunoglobulin M), is needed to test for infection, according to the Brazilian Ministry of Health [50] (Figure 3).

**Figure 3 figure3:**
[figure not shown]
Suspected vs confirmed cases of COVID-19. RT-PCR: real-time polymerase chain reaction, IgM: immunoglobulin M, IgA: immunoglobulin A, IgG: immunoglobulin G, ELISA: enzyme-linked immunosorbent assay, IC: ion channel, ECLIA: electrochemiluminescence immunoassay.

Moderate-to-severe cases are defined as those that require hospitalization, mechanical ventilation, or result in death. Through direct contact with hospitals, hospitalized patients are being clinically evaluated in terms of longitudinal follow-up and treatment outcome, infection severity, length of stay, need for intensive care, mechanical ventilation, and cause of death.

Considering the heterogeneous community viral transmission in Brazil, some epidemiological approaches were developed to assure a similar path involving patients with rheumatic diseases and controls, such as the same pandemic COVID-19 curve in each city and region [41]. Therefore, after initial contact (V1), two strategies were adopted to maintain the follow-up of patients and to optimize the capture of main outcomes. Firstly, an active strategy is addressed in cases of flu-like syndrome and symptoms suggestive of COVID-19. For this strategy, the patient or household member is shown how to provide clinical data on the patient or his/her control through a toll-free telephone number (the 0800 system). Secondly, the patient is contacted every week by the REDCap team to gather relevant data on infection. An additional visit is conducted if the patient or control provides information about flu symptoms or disease activity via an unscheduled phone call or contact through the toll-free number. In both cases the individual will be advised to stay home and use painkillers or an antipyretic. In case of worsening/severe symptoms (eg, persistent cough or fever and shortness of breath), they will be advised to visit a hospital or to make an appointment with a physician involved in our study.

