**Methods:**

This is a 24-week, prospective, observational cohort study comprising patients from public and private health services across Brazil, who chronically use antimalarials for the treatment of immune-mediated rheumatic diseases, osteoarthritis, or chikungunya-related arthropathy. A total of six sequential phone interviews were scheduled during the COVID-19 outbreak in five different regions of Brazil. Information regarding social, epidemiological, and demographic data, as well as details about rheumatic diseases, antimalarials, comorbidities, and concomitant medication, is being recorded using a specific online form in the REDCap database. Symptoms suggestive of COVID-19, including fever, cough, dyspnea, anosmia, and dysgeusia, are being self-reported and collected via phone interviews. Our main outcomes are hospitalization, need of intensive care unit, and death.

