## Discussion

This study’s novel design, with its large sample of chronic antimalarial users, will enable us to perform a thorough prospective assessment (every 2 weeks) to explore whether vulnerability to SARS-CoV-2 infection may be associated with IMRD or to hydroxychloroquine after adjustments for cofounders, especially those related to other immunosuppressive drugs and comorbidities. On the other hand, it has some limitations, such as compliance and adherence; a potential shortage of HCQ (hydroxychloroquine) in some parts of our country; possible biases associated with recalling symptoms; inability to answer the phone (due to hospitalization or death), and lack of confirmatory tests (PCR tests for SARS-CoV-2 or antibody-based RNA [ribonucleic acid]) for all enrolled patients and controls, especially in those with nonsevere forms. Future randomized controlled trials may provide a better understanding of these differences.

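### As written, weekly contact is scheduled for patients but not for controls, so a self-reported primary outcome is captured unequally and some deaths could go uncounted

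*Protocol article*

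**What the plan says.** In the Protocol article, Methods, Data Collection (text after Figure 3), two follow-up strategies after the first interview are introduced as a way to give patients and controls comparable follow-up.

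- The first relies on reports coming in: "the patient or household member is shown how to provide clinical data on the patient or his/her control through a toll-free telephone number".
- The second is scheduled: "Secondly, the patient is contacted every week by the REDCap team to gather relevant data on infection".
- The next sentence covers both groups again: "An additional visit is conducted if the patient or control provides information about flu symptoms or disease activity".
- Hospital follow-up is described as: "Through direct contact with hospitals, hospitalized patients are being clinically evaluated in terms of longitudinal follow-up and treatment outcome".

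On non-response, the same section says that interviews with those "who did not answer the telephone after three consecutive calls at intervals of 3 days were canceled". The person stays in the study, and the closing interview (V6) is planned whatever was missed before it. The Discussion lists as a limitation "inability to answer the phone (due to hospitalization or death".

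Contact frequency is described in two further places. The Abstract says "A total of six sequential phone interviews were scheduled", in a 24-week study. The Discussion speaks of a "thorough prospective assessment (every 2 weeks".

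The Outcomes section lists infection, from suspected upward, among the primary outcomes. The clinical case definition in Data Collection rests on self-reported symptoms and/or contact with a case.

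**The concern.** A symptom-based outcome depends on how often people are asked. If one group is asked weekly and the other is not, mild illness is recorded more completely in the first group. Here the more closely watched group would be the antimalarial users. The bias would therefore run against the study's hypothesis: it could mask protection or look like harm. Adjustment for age, sex, comorbidities, medications and vaccination cannot remove it, because contact intensity goes with group membership itself.

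A second, smaller problem concerns severe outcomes. The article names hospitalization and death as reasons for not answering, and both are main outcomes. For deaths in particular, the event can prevent the interview that would have recorded it.

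**Working it through.** **1. Who is covered by each source, as worded**

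| Source | Wording covers | Depends on |
|---|---|---|
| Six interviews | both groups (main outcomes are collected in both) | the person answering |
| Weekly contact | the patient | a scheduled call |
| Toll-free line | patient and control | the patient or a household member phoning in |
| Additional visit | patient and control | a report being made |
| Hospital contact | hospitalized patients | an admission becoming known |

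No sentence gives controls a scheduled weekly contact. Over 24 weeks, weekly contact gives 24 scheduled occasions to report against six interviews: 24/6 = 4. This compares occasions only if controls are not called weekly, and it is not a measure of bias.

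**2. Effect of unequal capture on the risk ratio**

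Observed rate = true rate × capture probability. With equal true rates, observed RR = capture in patients / capture in controls, whatever the true rate is. The documents give no capture rates, so those below are assumptions. The 20% true rate is borrowed from the Sample Size section, where it refers to moderate-to-severe disease; here it serves only as an illustration.

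Group sizes are the planned 3000:6000 and the enrolled 5166:5277 (10,443 − 5166 = 5277). The last two columns give the chance of a two-sided 5% result showing patients worse, when there is no true difference.

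| Capture, patients / controls | Observed rates | RR | 3000:6000 | 5166:5277 |
|---|---|---|---|---|
| 95% / 95% | 19.0% / 19.0% | 1.00 | nominal | nominal |
| 100% / 95% | 20.0% / 19.0% | 1.05 | 20.5% | 25.1% |
| 100% / 90% | 20.0% / 18.0% | 1.11 | 63.0% | 74.1% |
| 95% / 80% | 19.0% / 16.0% | 1.19 | 94.3% | 98.1% |

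Example, 100% / 90% at enrolled size: the difference is 0.02, the standard error about 0.00768, 0.02/0.00768 = 2.60, and 2.60 − 1.96 = 0.64, which gives a probability of about 0.74. A lower true rate leaves the RR unchanged and lowers these probabilities.

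**3. Comparison with the effect the study can detect**

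The Sample Size section gives 3000 users and 6000 nonusers, a 20% rate, α 5% and β 20%, but no effect size, so the figure cannot be reproduced forward. Solving back with the two-proportion formula (1:2, two-sided) gives about 17.55% against 20%, RR 0.877. As a check, 17.5% against 20% needs 2889 users.

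If a capture gap acted on an outcome of that size:

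- 100% / 95%: observed RR 0.877/0.95 = 0.923; power falls from 80% to about 39%.
- 100% / 90%: observed RR 0.877/0.90 = 0.975; power falls to about 8%.

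This is a yardstick only. Admissions and deaths should depend less on call frequency than mild symptoms do.

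**4. Severe events**

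Cancellation after three unanswered calls removes one interview. A survivor can still report an admission at V6; someone who died cannot. The deaths at risk are those found neither through hospitals nor through a household report. How much each one matters depends on the event count. At an assumed 1–2% severe rate, controls would have 0.01 × 5277 = 53 to 0.02 × 5277 = 106 events. At the article's own 20% they would have 0.20 × 5277 = 1055.

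**5. Contact schedule**

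Two-weekly contact over 24 weeks means 24/2 = 12 intervals. Six interviews spread evenly have five intervals of 24/5 = 4.8 weeks. Weekly contact could sit alongside six interviews, but the two-weekly description matches neither.

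**The case against.** The strongest reply is that the article uses the word patient loosely. The cancellation rule and the V6 commitment are also worded for patients, the paragraph aims at comparable follow-up, and outcomes are collected in both groups. The weekly call might gather data on the pair. A reader might infer that controls were certainly never called weekly; the text does not say so. What stands is that this paragraph names the control in the sentences before and after and leaves it out here, so the plain reading is unequal contact. The same looseness affects any remedy: V6 and hospital contact are common sources only if stated to include controls.

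A reader might also infer that severe cases are lost. The documents do not support that. The participant remains enrolled, V6 is planned regardless of missed interviews, hospitals are contacted directly, and a household member may phone in. The cancellation rule is not shown to differ by group, and similar loss in both groups would cost events more than it would bias the RR. The article also discloses non-answer as a limitation, and further tracing may be in the full protocol. What remains is a narrow gap for deaths. It may be wider for work-colleague controls, whose own households are not clearly covered by the reporting route.

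Finally, a reader might place six two-weekly interviews at weeks 0 to 10 and conclude that the remaining follow-up is uncovered. That conflicts with V6 being the closing interview of a 24-week study, and Figure 2, which holds the interview schedule, is not shown.

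**Conclusion.** The point holds in a limited form. As worded, surveillance between interviews is scheduled for patients and left to volunteered reports for controls, while a primary outcome depends on self-report. The direction, if the text was followed, is an inflated rate in patients. The size is unknown: assumed capture gaps of 5 and 10 percentage points from 100% give RRs of 1.05 and 1.11 with no true difference, which is comparable with the effect of about 0.88 that the sample size implies. The bias disappears if capture was equal.

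The consequence for hospitalization and death is smaller and confined to events that hospital contact and household reports both miss. The 1–2% severe rate is an assumption without a source in the article. The wording should be corrected before the groups are compared, but it does not invalidate the study.

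**What to change.** 1. **Equal sources.** Either ask about the control in the same weekly call, or base the primary patient–control comparison on V1–V6 and hospital contact, stated explicitly to include controls. Flag events found only through weekly patient calls and use them in a sensitivity analysis. If controls were in fact called weekly, saying so settles this part.
2. **Tracing after three failed calls, in both groups.** Obtain vital and hospital status, with dates, from the paired participant and count it.
3. **One schedule.** Reconcile the weekly, two-weekly and six-interview descriptions, saying which contacts apply to which group.

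Cost: one extra question or a call to someone already enrolled, and a source field in the database. Some dates will be proxy-reported. Enrolled controls average 5277/5166 = 1.02 per patient, so some patients may have no partner to ask. Timing limits the first option: enrolment closed on May 17, 24 weeks later is November 1, and the article appeared on October 14. For this cohort the common-source analysis and tracing at closing are the practical routes, and the source flag works only if the source of each report was recorded.

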### Outcomes

Primary outcomes (at baseline and during the 24-week study period) are as follows:

SARS-CoV-2 infection (illness): suspected, suggestive, or confirmedDeathHospitalizationNeed for intensive care unitNeed for mechanical ventilationTotal hospitalization timeDate of occurrence of an adverse event (eg, death, hospitalization)

Secondary outcomes are as follows:

General clinical differences in COVID-19 course severity between rheumatic patients and nonrheumatic controls;Initial clinical differences and progression to moderate or severe course of disease between the two groups.

Confounding and adjustment variables are age, sex, comorbidities, concomitant medications, and flu vaccine.

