### Control Group

The control group will consist of healthy individuals aged >18 years, who are household cohabitants or work colleagues of patients with rheumatic diseases in the intervention group.

Contact with a suspected or confirmed case of COVID-19 is defined as an individual sharing accommodations with a patient with a rheumatic disease (eg, residing in the same house or environment as roommates, occupational colleagues, etc). The exposure grade assessment is individualized, considering the type of environment and the exposure time.

For each case, two household and/or professional contact individuals will be selected as controls. The choice of the first control is prioritized by flu-like symptoms and defined as the “symptomatic group,” including suspected or confirmed cases. Those without symptoms will comprise the “asymptomatic group;” both household and/or contact individuals can be selected, preferably paired for age and sex.

The household and/or workplace contacts were chosen to characterize the control group because of their high epidemiological value during community viral transmissions worldwide, instead of including nonusers of antimalarials with rheumatic diseases. Moreover, lupus patients without antimalarial treatment are quite uncommon, except in those with previous toxicity (maculopathy, allergy, long-term remission, etc).

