### Statistical Analysis

The data will be analyzed using descriptive statistics—absolute and relative frequencies for categorical variables and quantitative measures (mean, quartiles, minimum, maximum, and standard deviation) for numerical variables. The normality of the data will be verified using the Kolmogorov-Smirnov test.

A chi-square test will be used to assess the association between categorical variables with standardized adjusted residual calculation; Fisher exact test will be used for small samples. The linear associations between two variables of a numerical nature will be evaluated using Pearson correlation.

To evaluate the behavior of clinical variables between two points in time by group, analysis of variance (ANOVA) will be used, with repeated measures. In the case of nonnormality of data, the means of the groups at each time point will be compared using the Kruskal-Wallis nonparametric test. To compare the means between phone visits in each group, the Wilcoxon nonparametric test will be used.

The comparison between the means of numerical variables with normal distribution will be verified through the Student *t* test. If the assumption of normality is violated, the Mann-Whitney nonparametric test will be used.

Adjusted multiple linear regression models will be used to assess the simultaneous effects of sex, age, duration of illness, comorbidities, concomitant medications, and other confounding variables, according to group and predefined outcomes. For dichotomous dependent variables, a logistic regression model will be preferred. Survival analysis models, including log rank and Kaplan-Meier tests, adjusted for confounding variables, will be developed to assess the main outcomes over time. The time defined as the end date will be the date of a major event, such as illness with confirmation or suspicion of infection, hospitalization, or death.

Correlation analysis will be performed using the Pearson test to assess the relationship between the incidence rate of confirmed COVID-19 cases per 100,000 inhabitants and the proportion of symptomatic patients and controls in municipalities. Data of confirmed cases per municipality are available through the Brasil.io project [51]. The QGIGS Desktop 3.6.0 (Open Source Geospatial Foundation) will be used for map plotting.

SPSS, version 20 (IMB Corp) will be used in all analyses, and a *P* value <.05 will be considered significant.

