## Results

This study is in the data collection phase. Study recruitment opened in March 2020. In an 8-week period (from March 29 to May 17), a total of 10,443 individuals enrolled at baseline (including 5166 patients with rheumatic diseases) from 23 tertiary rheumatology centers in 97 Brazilian cities. Data analysis is scheduled to start after all relevant data have been collected.

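### The protocol gives two different adjustment sets, and the only closed one omits smoking, social characteristics and exposure grade, so confounding by them may remain and the set could be chosen after seeing the data

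*Protocol article*

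**What the plan says.** The Outcomes section closes with a definite list: "Confounding and adjustment variables are age, sex, comorbidities, concomitant medications, and flu vaccine".

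The Statistical Analysis section describes the regression models differently. They are to assess the "simultaneous effects of sex, age, duration of illness, comorbidities, concomitant medications, and other confounding variables, according to group and predefined outcomes". The time-to-event analyses are "Survival analysis models, including log rank and Kaplan-Meier tests, adjusted for confounding variables", with no variables named.

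Other sections show what else is available:

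- Data Collection: "Data are being collected regarding social, epidemiological, and demographic characteristics", and "aspects related to comorbidities, smoking, alcohol intake, and concomitant medications are being recorded".
- Control Group: "The exposure grade assessment is individualized, considering the type of environment and the exposure time".
- Results: participants come "from 23 tertiary rheumatology centers in 97 Brazilian cities", so place is known.

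Geography is addressed through the design. Controls are people who live or work with the patient, and the text after Figure 3 says the aim was a similar path for both groups, "such as the same pandemic COVID-19 curve in each city and region". In the planned analyses, municipality appears only in a correlation of local incidence with the proportion symptomatic, and in maps.

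**The concern.** This is a non-randomised comparison of patients with rheumatic disease who take antimalarials against contacts who have neither the disease nor the drug. Pairing is only a preference and covers only age and sex. Sharing a home or workplace does not make two people behave alike: a patient with a chronic disease, perhaps on immunosuppressants, may isolate more than a contact does. Lower exposure would then be a direct rival explanation for fewer cases among antimalarial users. Smoking and social position could also differ between the groups.

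The two lists create a second problem. If the Outcomes list governs, these factors are left out. If the Statistical Analysis wording governs, they may be included, but nothing says which ones, and the choice could follow the results. The extra item, duration of illness, also has no meaning for healthy controls if it refers to the rheumatic disease.

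**Working it through.** **1. The two lists side by side**

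| Variable | Outcomes | Statistical Analysis |
|---|---|---|
| Age, sex, comorbidities, concomitant medications | named | named |
| Flu vaccine | named | not named |
| Duration of illness | not named | named |
| Unspecified further confounders | no | yes |
| Smoking, social characteristics, exposure grade, place, entry date | not named | not named |

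**2. The effect the study is sized for**

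Inputs from the Sample Size section: 20% event rate, one user to two nonusers, about 3000 and 6000, α = 5%, β = 20%. No effect size and no sidedness are given, so the sample size can only be solved backwards. I take 20% as the control rate.

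n(users) = [z(α)·√(1.5·p̄(1−p̄)) + z(β)·√(p₁(1−p₁) + p₀(1−p₀)/2)]² / (p₁−p₀)²

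Two-sided, with p₀ = 0.20 and p₁ = 0.1754:

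- p̄ = (0.1754 + 2 × 0.20)/3 = 0.1918
- numerator = (1.96 × 0.4822 + 0.8416 × 0.4740)² = 1.806
- n = 1.806/0.0246² ≈ 2985

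The implied risk ratio is 0.1754/0.20 = 0.88. With continuity correction, p₁ = 0.1752 gives n = 2997, again 0.88. One-sided, p₁ = 0.1781 gives n = 2978 and a ratio of 0.89.

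**3. What one omitted factor could do**

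For a binary factor that multiplies risk by R, with prevalence q₁ in users and q₀ in controls, and no drug effect:

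spurious RR = [1 + q₁(R−1)] / [1 + q₀(R−1)]

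R, q₁ and q₀ are all assumptions; the article gives none of them.

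| R | q₁ vs q₀ | Spurious RR |
|---|---|---|
| 2.0 | 30% vs 60% | 1.30/1.60 = 0.81 |
| 2.0 | 30% vs 40% | 1.30/1.40 = 0.93 |
| 2.0 | 20% vs 40% | 1.20/1.40 = 0.86 |
| 1.5 | 30% vs 60% | 1.15/1.30 = 0.885 |
| 1.2 | 10% vs 15% | 1.02/1.03 = 0.99 |
| any | equal | 1.00 |

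Setting these beside 0.88 further assumes that exposure acts on moderate-to-severe disease in proportion to its action on infection.

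**4. Place**

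The Results section gives 10,443 enrolled, of whom 5166 are patients, so 10,443 − 5166 = 5277 others. That is 5277/5166 = 1.02 per patient against the planned 2. Take two cities with equal numbers of patients, assumed event rates of 5% and 20%, and no drug effect. The patient rate is then (5% + 20%)/2 = 12.5%.

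- Same control:patient ratio in both cities: the control rate is also 12.5%, RR 1.00.
- Ratios 0.8 and 1.2: control rate (0.8 × 5% + 1.2 × 20%)/2.0 = 14%, RR 0.125/0.14 = 0.89.
- Ratios 1 and 2: control rate (1 × 5% + 2 × 20%)/3 = 15%, RR 0.125/0.15 = 0.83.

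Place therefore matters in an unmatched analysis only if the ratio varies between places. The article does not report whether it does.

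**The case against.** The strongest reply is that the Statistical Analysis section leaves the set open and excludes nothing, and that a journal article normally leaves the full covariate list to the analysis plan. A reader might infer from the Outcomes list that avoidable confounding certainly stays in the comparison. The documents do not support that, because the open clause could admit every omitted item. The article does, however, state a closed list in one section and a conflicting one in another. That is a fault in what is written, not a detail left for later.

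Three further points stand, at least in part:

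- **Place and time.** Drawing each patient's own contacts, within one recruitment window (29 March to 17 May), balances much of this by design, and household members share some social characteristics. A reader might infer that city is a proven omitted confounder. It is not; it can bias only through a varying control:patient ratio. With enrolment near 1:1 instead of 1:2, such variation is plausible but not shown.
- **Exposure grade.** A reader might infer that it is already measured in both groups at baseline. The sentence sits in the Control Group section and the data form is not shown, so this cannot be confirmed. A grade reflecting contact during follow-up would need a baseline definition before being used for adjustment.
- **Conditioning on the contact set.** This is not free. It uses only sets with discordant outcomes, which at about 1:1 enrolment and with outcomes such as death could discard much information.

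Greater isolation by patients is also conjecture, since the article reports no difference in behaviour.

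**Conclusion.** The point holds in a limited form. The article gives two adjustment sets that disagree, and the only closed one omits smoking and social characteristics, which are recorded, and exposure grade, which is assessed. Confounding by these factors may remain, and the final set is open to choice after the data are seen.

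The possible size ranges from negligible (0.99) to as large as the whole effect sought (0.81 to 0.93 in the main illustration, against about 0.88). The 0.88 is back-calculated and should not be read as the plan's own target. The bias figures show what assumed imbalances would do; they are not estimates of bias in this cohort. It is worth correcting before analysis because the remedy is cheap.

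**What to change.** Before analysis starts:

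1. Reconcile the Outcomes and Statistical Analysis sections into one named adjustment set for the main logistic and survival models. Say whether flu vaccine and duration of illness belong, and define the latter for controls or drop it from the between-group models.
2. Add smoking and social variables. Add exposure grade as measured at baseline in both groups, if the form records it so.
3. Include municipality or region and calendar week of entry as strata or covariates.
4. Allow for the patient-contact cluster with robust or mixed-model errors. Keep strict conditioning on the contact set as a sensitivity analysis.

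The Results section says analysis begins only after data collection, so this is mainly a change of wording and a few more model terms. For rare outcomes such as death, some terms may have to be collapsed, for example municipality into region. The plan should say so in advance.
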